#### Secondary objectives

• To evaluate the effect of the addition of a faeces collection paper to the iFOBt-kit on the participation rate;

• To compare participation rates between the first and second round;

• To compare the participation rates in groups that were defined as participants or non-participants in the first round;

• To evaluate the diagnostic yield (detection rates of cancer, high-risk adenoma and low-risk adenoma) and complication rate of iFOBt and colonoscopy and to compare these to results of the first screening round;

• To compare the baseline characteristics of participants and non-participants;

• To evaluate factors influencing the decision to participate;

• To evaluate invitees' ability to make a well-informed decision to participate;

• To evaluate participants' experience with the screening program in terms of their perception and the burden of the iFOBt;

• To evaluate the psychological impact on participants of receiving a positive test result;

• To evaluate the burden of the colonoscopy in iFOBt positives;

### Study design and randomization

The study design is a cohort study examining the participation rate of a second round of FOBt screening. Within the cohort study a randomized controlled trial will be executed comparing the use of a collection paper versus no collection paper on the participation rate. All persons eligible for invitation are pre-randomized to one of both groups before informed-consent is obtained. Through randomization, non-responders to the previous round, responders to the previous round and first-time invitees will be equally distributed over both study groups.

### Study population

Our study population consists of 10.000 average risk persons between 50 and 75 years of age with the postal code of our target area. The target area of the second round is identical to the target area of the first round and is selected because it had an average uptake in the nationwide breast cancer screening program. Thus, among the invitees of the second round 3 different groups can be identified: 1) non-responders to the first round; 2) responders to the first round; 3) first-time invitees (persons aged 50–75 that moved into the target area or persons that turned 50 within the last 2 years).

Institutionalized people will be excluded from participation. Responders to the first round that tested positive in the first round and had a follow-up colonoscopy will not be re-invited. They will be advised follow-up conform the national guidelines on surveillance colonoscopy[12].

Other exclusion criteria are CRC symptoms in the last three months (rectal blood loss and/or changed bowel habits and/or unintentional weight loss). These symptomatic persons will be advised to contact their general physician and not to participate in the study. Also, persons with a life-expectancy of less than 5 years and persons that have undergone a colonoscopy in the previous 2 years will be excluded from participation.

### Invitation procedure

Invitation will take place from August 2008 until June 2009. The screening program uses a centralized invitation procedure and all invitations will be sent out by the regional Comprehensive Cancer Centre Amsterdam. This institution is also involved in the organization of other population-based cancer screening programmes in the region including breast and cervical cancer screening. All persons will receive an invitation kit by postal mail containing an invitation letter, an information leaflet, an immunochemical FOBt, a test instruction and a frequently asked questions card. A collection paper to facilitate the collection of faeces will be enclosed in half of the invitation kits.

A reminder will be sent after two and eight weeks.

### Information leaflet

The information leaflet is an updated version of the leaflet that was used in the first round. The main difference is that it is adjusted following the principle of informed choice. This principle states that in order to enable a person to make a well-informed decision to participate in a screening program or not, certain information has to be available to this person. The information that was already present in the previous leaflet is optimized and covers all information relevant to colorectal screening: details of CRC, details of the iFOBt, possibility of false-negative and false-positive results, details of the follow-up investigation colonoscopy, prognosis and treatment options, and details of benefits and harms. Also, the freedom of choice to participate in the program or not is emphasized.

### iFOBt

The iFOBt that will be used in this study is the OC-sensor (Eiken Chemical Co, Tokyo, Japan). This is the same iFOBt that was used in the first round. This is a clinical laboratory-based, automated, immunochemical test that measures human haemoglobin content of a stool sample. No diet restrictions are necessary before performing the test.

The iFOBt consists of a sampling bottle with a sampling probe attached to the cap. Participants are instructed to collect the faeces sample by scraping the probe over a broad area of the stool surface. After the sample is taken, the probe is reinserted into the sampling bottle. By reinserting the probe, the fecal sample is suspended in haemoglobin-stabilizing buffer. Participants are instructed to keep the bottle in a dark and cool place and to return it as soon as possible.

Returned iFOBts will be collected at the specialized laboratory of the AMC and will be processed by quantitative haemoglobin analysis by the OC-MICRO automated instrument using a 50 ng Hb/mL threshold to determine positivity.

### Collection paper

All persons randomized to the collection paper group will receive a floating collection paper (Eiken Chemical Co, Tokyo, Japan) with their iFOBt. This is a biodegradable disposable paper float that has to be placed in the toilet bowl to immobilize the stool for easy sampling.

### Informed consent

Written informed consent will be obtained from all participants before analyzing the stool sample. Enclosed in the invitation kit is an informed consent form that participants are asked to return together with the test bottle. Test bottles will not be processed in the absence of a signed informed consent. When the informed consent is lacking, a notification will be sent to the participant together with a request to return the informed consent form.

### Provision of test results

All specimens will be analyzed in a specialized laboratory. Participants will receive the test result by postal mail. A positive test result is defined as an Hb content of 50 ng/mL or more. In this case the participant will be invited for a consultation at the colorectal screening centre in the AMC to discuss the recommended follow-up investigation: the colonoscopy. In case of a negative test result no follow-up is needed. In case of a positive test result, the general practitioner will also be informed.

### Follow-up colonoscopy

During the consultation at the colorectal screening centre, information is given on the consequences of the positive test result. In absence of any contraindications a colonoscopy will be advised and all relevant information on this examination (technique, risks and alternatives) will be given. If the participant consents, a colonoscopy will be performed within two weeks after the consultation.

Colonoscopy is considered the clinical reference standard for detection of adenomatous polyps and CRC. The procedure will be performed in our screening centre according to quality guidelines, adapted from the recently published guidelines of the American Society for Gastrointestinal Endoscopy[13]. In case of polyps or cancer, endoscopic removal of the lesion will be attempted during the same procedure. If immediate endoscopic treatment is impossible, biopsies will be obtained and pathological assessment of these tissue samples will provide definitive diagnosis so further treatment can be initiated.

### Lesions

Of all lesions, data on location (centimetres from anus, segment of the colon), size (millimetres) macroscopic aspect (hyperplastic, adenomatous, carcinomatous), morphology (sessile, pedunculated, flat, depressed), diagnostic or therapeutic procedure (total polypectomy, piecemeal polypectomy, biopsy), use of saline and/or epinephrine), and macroscopic involvement of margins will be recorded during the colonoscopy.

### Pathology

One experienced gastrointestinal pathologist will evaluate all samples. Of each lesion the histology (hyperplastic polyp, serrated adenoma, tubular adenoma, tubulovillous adenoma, villous adenoma or carcinoma,) and grade of dysplasia (low- or high-grade) will be assessed according to the Vienna classification.

### Follow-up after colonoscopy

The findings at colonoscopy will be discussed two weeks after the colonoscopy through a consultation by telephone or at the outpatient clinic. A confirmation of the colonoscopy result will be sent by postal mail. In case of a negative colonoscopy, no follow-up is needed. Follow-up of patients after removal of adenomatous polyps or cancer will be performed by surveillance colonoscopies according to the Dutch CBO consensus[12]. Cases of CRC will be referred for appropriate management (e.g. consultation of a surgeon). The general practitioner will also receive a report of the colonoscopy procedure.

### Questionnaires

#### Socioeconomic and demographic characteristics

Baseline characteristics as age, marital status, education, employment and ethnicity will be recorded by a questionnaire two weeks after the invitation is sent.

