#### Informed choice

Informed choice (knowledge and attitude) will be measured at baseline.

To evaluate whether the principle of informed choice applies, it is necessary to understand the knowledge, attitude and behaviour of the invited persons. The decision to participate in screening will be classified as an informed choice if: a) the participant has a positive attitude towards undergoing a test; b) the participant has relevant knowledge about the test. Knowledge is considered relevant if it covers 12 general domains. (These domains are applicable to all types of mass screening and are adapted from the Dutch prenatal screening for Down syndrome[14]) and c) this person actually undergoes the test. The decision not to participate in screening will be classified as an informed choice if: a) an individual has a negative attitude towards undergoing a test; b) an individual has relevant knowledge about the test; and c) this person does not undergo the test. All choices that occur when individuals do not have relevant knowledge or when their attitudes are not reflected in their behaviour are to be considered uninformed[15].

Knowledge about screening with iFOBt will be measured using 24 statements derived from expert opinion and information obtained in the first screening round, with two response options (e.g. "the fecal occult blood test has to be repeated every 2 years" [correct-incorrect]). The number of correct items is used as the knowledge score. Attitude regarding undergoing screening will be measured by 4 items, each scored on a 7-point scale (e.g. "for me, having the screening test for colorectal cancer would be...." [a good idea-a bad idea]. Attitude items are based on the Marteau's measure of informed choice[15]. Screening behaviour is measured by either participation or non-participation in the present study (i.e. returning of the iFOBt).

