#### Reasons for (non)participation

Reasons for (non)participation will be collected in all invitees at baseline.

For the present study the Health Belief Model (HBM)[16] will be used as theoretical background to understand reasons for (non-)participation. This model is widely used to explain cancer screening adherence. The HBM states that health behaviour depends on an individual's desire to avoid illness and the belief that a specific action will prevent illness. Key factors in explaining health behaviour are: perceived susceptibility, perceived severity, self-efficacy, perceived benefits, perceived barriers. Reasons for (non)participation will be measured by eight items scored on a 4-point scale (e.g. "I think I have a higher chance of having colorectal cancer than other people my age..." [totally agree-totally disagree]. These questions are supplemented with 12 questions used in the first screening round (e.g. "I find that performing the FOBt is disgusting..." [agree – not agree].

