#### Psychological consequences of a positive FOBt

Psychological consequences of screening will be documented in all invitees at baseline and immediately before and 2 weeks after undergoing colonoscopy in participants with a positive FOB test result.

The psychological consequences of receiving a positive FOB test result will be measured with the validated Dutch version of the 'Psychological Consequences of screening Questionnaire' (PCQ)[17]. The English version of this questionnaire has successfully been used in various screening studies[18]. The PCQ consists of three subscales: emotion (5 items), physical dysfunction (4 items) and social dysfunction (3 items). Scores on all items vary between 0 (not at all) and 3 (often) (e.g. "during the past week I had problems sleeping..." [not at all – often].

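### The only dated baseline questionnaire follows the test kit by two weeks, so some attitude reports probably post-date the test and some baseline PCQ scores may post-date a positive result

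*Protocol article*

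**What the plan says.** All references are to the protocol article.

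- **Invitation procedure:** the posted kit holds "an invitation letter, an information leaflet, an immunochemical FOBt, a test instruction and a frequently asked questions card", and in half of the kits a collection paper. Informed consent adds a consent form. No questionnaire is listed. On follow-up mailings: "A reminder will be sent after two and eight weeks".
- **iFOBt** and **Provision of test results:** participants are asked to return the bottle without delay, and results go out by post. No turnaround time is given, and nothing makes the result wait for a completed questionnaire.
- **Socioeconomic and demographic characteristics:** baseline characteristics "will be recorded by a questionnaire two weeks after the invitation is sent". This is the only date attached to any baseline form.
- **Informed choice:** "Informed choice (knowledge and attitude) will be measured at baseline". A choice counts as informed only if knowledge is sufficient and attitude agrees with whether the test was returned.
- **Reasons for (non)participation:** "Reasons for (non)participation will be collected in all invitees at baseline".
- **Psychological consequences of a positive FOBt:** the PCQ "will be documented in all invitees at baseline and immediately before and 2 weeks after undergoing colonoscopy", the last two in positives only. The sample item looks back one week: "during the past week I had problems sleeping".
- **Data analysis:** a multivariate analysis is to relate questionnaire variables to participation.

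**The concern.** Knowledge and attitude are collected to judge whether the decision to test was well informed, so they should describe the invitee before that decision. The baseline PCQ should likewise describe a positive participant before the result. A form sent two weeks after the kit secures neither.

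The timing is also uneven. A prompt participant answers after acting. A late participant answers before acting, and an undecided invitee answers around the first reminder. The order of attitude and behaviour therefore depends on the behaviour being classified, and participants and non-participants are not compared on equal terms.

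Three uses of the data are exposed: the objective on well-informed decisions, the objective on the psychological impact of a positive result, and the multivariate analysis, where some explanatory variables would be measured after the outcome they are meant to explain.

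**Working it through.** **1. No stated figure to reproduce.** The article gives no number for questionnaire timing, informed choice or PCQ change. Its sample-size precision concerns participation only: 1.96 × √(0.25/10,000) = 0.0098, which agrees with the stated 1% and does not depend on the questionnaires.

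**2. Order of events as written.** Kit with test sent (week 0) → prompt return requested → result posted when available → baseline form at two weeks, when the first reminder is also due → second reminder at eight weeks. An invitee who complies promptly can have tested before the form is sent. Knowing the result by then also requires signed consent on file, analysis and a posted letter.

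**3. Shared date.** Only the demographic form is dated. The other instruments are placed at baseline without a date, and no other baseline mailing is described. A common date is the natural inference, but it is not stated.

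**4. Informed choice, illustration only.** Let k be the knowledgeable share of participants, m the share of these whose attitude before testing disagreed with their behaviour, s the share of forms completed after the test, and c the share of disagreeing attitudes that shift to agree.

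Excess in informed choice among all participants = k × m × s × c.

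All values are assumed: m = 15%, c = 50%, s = 30% to 60%.
- Within knowledgeable participants (k = 1): 0.15 × 0.5 × 0.3 = 2.25 points, to 0.15 × 0.5 × 0.6 = 4.5 points.
- Among all participants with k = 60%: 0.6 × 2.25 = 1.35 points, to 0.6 × 4.5 = 2.7 points.

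A cruder form takes a true informed share f and lets a share c of all uninformed choices be reclassified when the form follows the test: observed share = f + (1 − f) × s × c.
- Low end (f = 0.70, s = 0.2, c = 0.1): 0.70 + 0.30 × 0.02 = 0.706, an excess of 0.6 points.
- High end (f = 0.50, s = 0.8, c = 0.3): 0.50 + 0.50 × 0.24 = 0.62, an excess of 12 points.

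This form is generous, because a change of attitude cannot repair missing knowledge.

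**5. PCQ, illustration only.** Let q be the share of positives who already know their result at baseline and already score at the full raised level. Observed mean change = (1 − q) × true change.

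| q (assumed) | Observed share of true change |
|---|---|
| 5% | 95% |
| 10% | 90% |
| 25% | 75% |
| 50% | 50% |

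The two later PCQ measurements in positives both follow the result, so the baseline is the only one that can precede it.

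**The case against.** **The shared date is inferred.** Correct. A fuller questionnaire schedule may exist outside the article. The inference still stands as the reading of this text, because every other instrument is called baseline and only one baseline date is given. If the instruments are sent at another time, stating it would settle the point.

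**How many people are affected is unknown.** Correct. The documents give neither a distribution of return times nor a laboratory turnaround. Knowing a positive result within two weeks takes several steps, and bottles without signed consent are not processed. A reader might infer that many participants answer after testing, or that 20% to 50% of the PCQ effect is lost. Neither is supported.

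**The direction is not certain.** This stands in part. Forgetting the leaflet could lower knowledge scores, and an unpleasant test could worsen attitude; both would work against inflation. Attitudes stated after an act may be expected to agree with it, so inflation is the likelier direction, but only that.

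**The PCQ argument presumes a change from baseline.** The article lists PCQ time points but no such analysis. Positives before colonoscopy could instead be compared with the baseline of all invitees, few of whom would know of a positive result. Blunting therefore applies only if a within-person change is used.

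**The main results are untouched.** Agreed. A reader might extend the concern to the participation rate or the collection-paper comparison. Both rest on test return and do not use the questionnaire scores.

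**Conclusion.** The concern holds in a limited form. Followed as written, the schedule lets some participants report attitude after testing, and some positives complete the baseline PCQ after learning their result. Agreement between attitude and behaviour is then likely inflated among participants, and any PCQ change from baseline likely blunted.

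The sizes above show how the effects would scale, but they are not estimates, since every rate in them is assumed. In particular, 2.25 to 4.5 points applies only to knowledgeable participants and is not the error in the overall informed-choice share.

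The conclusion rests on three assumptions: the undated instruments share the two-week date, no unstated instruction requires the form to be completed before sampling, and results are not held back. It concerns secondary objectives and deserves correction because, without completion dates, the two situations cannot be separated afterwards.

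**What to change.** 1. State when knowledge, attitude, reasons and PCQ are collected, if not with the demographic form.
2. Record the completion date of every form and link it to the test-return and result-letter dates. The article does not say that these dates are kept, so their recording should be specified too.
3. For positives, accept as PCQ baseline only forms completed before the result letter.
4. Keep all forms in the overall informed-choice estimate. As a pre-specified sensitivity analysis, report participants separately by completion before or after test return, and label post-return attitudes as post-decision.
5. Apply the same split where questionnaire variables enter the multivariate analysis of participation.

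Pre-return forms should not become the main informed-choice estimate. That would drop prompt participants while keeping every non-participant, so selection would depend on the outcome. Moving the questionnaire closer to the kit is not proposed either, because it could itself influence participation, the primary outcome.

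**Cost:** one date field, the linkage and a few lines of analysis text. Fewer PCQ baselines will be usable, and forms completed before return or before the result over-represent slower returners. The report should say so.

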#### Informed choice

Informed choice (knowledge and attitude) will be measured at baseline.

To evaluate whether the principle of informed choice applies, it is necessary to understand the knowledge, attitude and behaviour of the invited persons. The decision to participate in screening will be classified as an informed choice if: a) the participant has a positive attitude towards undergoing a test; b) the participant has relevant knowledge about the test. Knowledge is considered relevant if it covers 12 general domains. (These domains are applicable to all types of mass screening and are adapted from the Dutch prenatal screening for Down syndrome[14]) and c) this person actually undergoes the test. The decision not to participate in screening will be classified as an informed choice if: a) an individual has a negative attitude towards undergoing a test; b) an individual has relevant knowledge about the test; and c) this person does not undergo the test. All choices that occur when individuals do not have relevant knowledge or when their attitudes are not reflected in their behaviour are to be considered uninformed[15].

Knowledge about screening with iFOBt will be measured using 24 statements derived from expert opinion and information obtained in the first screening round, with two response options (e.g. "the fecal occult blood test has to be repeated every 2 years" [correct-incorrect]). The number of correct items is used as the knowledge score. Attitude regarding undergoing screening will be measured by 4 items, each scored on a 7-point scale (e.g. "for me, having the screening test for colorectal cancer would be...." [a good idea-a bad idea]. Attitude items are based on the Marteau's measure of informed choice[15]. Screening behaviour is measured by either participation or non-participation in the present study (i.e. returning of the iFOBt).

